## Abstract

**Background:** Peripheral nerve injuries are common, with approximately 9,000 cases in the UK annually. Young working individuals are predominantly affected, leading to significant health and social implications. Functional recovery is often poor with impaired hand sensation, reduced motor function and pain and cold intolerance. Where a nerve gap exists, nerve grafting remains the gold-standard treatment but creates a second surgical site, sensory deficit at the donor site, possible neuroma formation and has limited availability. Current commercially available synthetic and resorbable nerve conduit alternatives are reported to be rigid and inflexible. This study will set out to examine the first-in-man use of a new nerve conduit device ‘Polynerve’ to repair small nerve gaps in digital sensory nerves of the hand. Polynerve is a degradable co-polymer of poly-ε-caprolactone and poly-l-lactic acid, which is shaped as a cylinder that has greater tensile strength, flexibility and less acidic degradation compared with current commercially available synthetic nerve conduits. In addition, it has a novel micro-grooved internal lumen that aids Schwann cell ingress and alignment to improve nerve regeneration.

**Methods: **In total, 17 eligible participants will be recruited to undergo repair of a transected sensory nerve of the hand using the Polynerve device. All participants that receive the nerve conduit device will be followed for a period of 12 months post-surgery. The primary endpoint is safety of the device and the secondary endpoint is degree of sensory nerve regeneration through the conduit assessed using standard sensory testing (2-PD, WEST monofilament testing and locognosia).

**Discussion: **The ‘UMANC’ trial is a single-centre UK-based, prospective, unblinded, phase I clinical trial of a novel nerve conduit device. We aim to demonstrate the safety of Polynerve as a synthetic, biodegradable nerve conduit and improve the treatment options available to patients with significant nerve injuries.

**Registration: **Clinicaltrials.gov:
NCT02970864; EudraCT: 2016-001667-37.

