## Primary objective

To assess the safety and tolerability of use of the polymer biomaterial nerve conduit to repair a sensory nerve transection of the hand.

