### Sample size

As this was a phase I study, primarily assessing safety of the device, a pragmatic decision on achievable recruitment numbers at a single centre who would be able to complete 12-months follow-up was made, and no formal power calculations were performed. The trial will recruit 17 participants over 12 months at an intended rate of approximately 1 to 2 participants per month. All participants fitting the eligibility criteria will be recruited.

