### Data collection

***Primary outcome.*** The primary outcome is safety following implantation of the Polynerve device. Safety will be assessed based on assessment of the number and degree (based on the Clavien-Dindo classification of surgical complications
^25^) of adverse device effects (ADE) that may occur during the study period
^26^. In order to ensure all ADE are captured, all adverse events (AE) will be assessed and recorded by the P.I. or appropriate co-investigator deputized by the P.I., immediately upon notification to the study team. (A full out-of-hours AE reporting facility is made available to all trial participants following implantation of a study device.)

The investigator will assess causal relationship between the medical device under investigation and each AE.

All expected AE/ADEs of grade 3 or above, except infection of the wound any occurrences of grade 2 or above, will be recorded as a serious AE (SAE) or serious ADE (SADE). Appropriate SAE reporting procedures will be followed including sponsor, MHRA and REC reporting—this will be overseen by a Trial Management Group (TMG).

The following variables will be collected in the case report forms (CRFs) for each ADE:

ADE diagnosis/descriptionThe date of ADE onset and dateClavien-Dindo grade of maximum intensityWhether the ADE is serious or not (see above)Assessment of relatedness to device under investigation or other procedure.Outcome

Safety information and all concomitant medications (that are associated with the surgical procedure) will be reviewed at each follow up visit (
Table 2).

At the end of the study data from initial treatment will be combined in the presentation of safety data. The number of participants experiencing each ADE will be summarised. The number and percentage of participants with ADEs in different categories (e.g. causally related, Clavien–Dindo ≥3 etc) will be summarised by group. SAEs/SADEs will be summarised separately if a sufficient number occur. Any ADE occurring within the defined 12-month follow-up period will be included in the ADE summaries.

***Secondary outcome.*** To measure degree of efficacy of the nerve conduit device, standard sensory outcome measures will be used:

two-point discrimination (2PD)
^27^,the Weinstein Enhanced Sensory Test (WEST)
^28^,Locognosia test (adapted methodology from Jerosch-Herold
*et al.* JBJSB 2006)

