### Statistical methods

Demographic data will be tabulated. All primary outcome data will be described and summarised. Secondary outcome measurement data will be tabulated and mean ± SD of static 2PD, WEST and Locognosia compared to contralateral control nerves will be presented with one-way ANOVA analysis between groups.

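### The abstract aims to demonstrate safety, but the objective and the descriptive single-arm design with 17 participants can only assess it: even 0/17 events allows a true risk of up to 16.2% (one-sided) or 19.5% (two-sided)

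*Protocol article*

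**What the plan says.** The protocol article states the purpose of the trial at two strengths.

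- **Abstract, Discussion paragraph:** "We aim to demonstrate the safety of Polynerve as a synthetic, biodegradable nerve conduit and improve the treatment options available".
- **Primary objective:** "To assess the safety and tolerability of use of the polymer biomaterial nerve conduit to repair a sensory nerve transection of the hand".

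The rest of the plan for the primary outcome is descriptive.

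- **Sample size:** "The trial will recruit 17 participants over 12 months at an intended rate of approximately 1 to 2 participants per month". The number rests on "a pragmatic decision on achievable recruitment numbers at a single centre", and "no formal power calculations were performed".
- **Data collection, primary outcome:** safety is judged by the number and Clavien-Dindo grade of ADEs over 12 months. "The number of participants experiencing each ADE will be summarised". "The number and percentage of participants with ADEs in different categories", such as causally related or grade 3 and above, is also to be tabulated.
- **Statistical methods:** "All primary outcome data will be described and summarised".

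The article gives no acceptable ADE rate, no success criterion and no hypothesis for the primary outcome.

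**The concern.** To demonstrate safety, a trial needs something to demonstrate it against: a rate judged acceptable, a comparator or a criterion. To assess or describe safety needs none of these. The abstract makes the stronger promise, while the primary objective and everything under it deliver the weaker one.

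What is at stake is the conclusion. The trial will be the first use of this device in humans, and the abstract is the part most widely read. A result of no or very few events in 17 would be good news, but it would leave a wide range of true risks open. A bare percentage such as 0% or 5.9%, set beside an aim of demonstrating safety, invites the reader to take more from the result than it holds.

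**Working it through.** **Inputs**

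- n = 17, one arm (Sample size; Study design).
- Outcome: the proportion of participants with a given category of ADE within 12 months (Data collection).
- Confidence level, sidedness and acceptable rate: none stated. This check assumes 95% and shows one-sided and two-sided limits.
- Observed count: the check takes zero events as the most favourable result possible, then one and two.

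**The plan's own figure.** There is no power or precision calculation to reproduce. The recruitment arithmetic is consistent: 17 / 12 = 1.4 participants per month, within the stated 1 to 2.

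**Upper limit when no event is seen (exact binomial).** With 0 of n events, the limit U solves (1 − U)^n = α.

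- One-sided 95%: U = 1 − 0.05^(1/17) = 0.162, or 16.2%.
- Two-sided 95% (Clopper-Pearson): U = 1 − 0.025^(1/17) = 0.195, or 19.5%.
- Cross-checks: the rule of three gives 3/17 = 17.6%; the Wilson two-sided upper limit is 1.96² / (17 + 1.96²) = 18.4%.

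**Two-sided exact 95% intervals for small counts**

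| Events | Percentage | Interval |
|---|---|---|
| 0/17 | 0% | 0% to 19.5% |
| 1/17 | 5.9% | 0.1% to 28.7% |
| 2/17 | 11.8% | 1.5% to 36.4% |

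**Chance of seeing no event at all, (1 − p)^17**

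| True risk p | Chance of 0/17 |
|---|---|
| 2% | 0.98^17 = 0.709 |
| 5% | 0.95^17 = 0.418 |
| 10% | 0.90^17 = 0.167 |
| 20% | 0.80^17 = 0.023 |

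So 17 participants without an event do exclude a risk of 20%, but only just. They say little about risks of 5% or 10%.

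**Denominator.** The Abstract describes 17 participants undergoing repair with the device, while Sample size speaks of recruiting 17. Entry is on clinical suspicion of a transected nerve (Table 1), and the conduit is used only when the gap found at operation is 5 to 20 mm (Intervention). If fewer than 17 were implanted, the limits would widen. With 14 implanted, an assumed figure, 0/14 gives 1 − 0.05^(1/14) = 19.3% and 1 − 0.025^(1/14) = 23.2%.

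**The case against.** The best defence is that the operative text never makes the strong claim. The disputed verb stands in the closing narrative line of the abstract. Objective, endpoint and analysis agree with one another and are all descriptive. The article says openly that this is phase I and that the number is pragmatic. The limits above would hold for any study of 17 people with no events. All of this stands, and it keeps the severity low.

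It also rules out several stronger readings that a reader might infer:

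- *That the trial will declare the device safe on 0/17 or 1/17.* The article contains no threshold, test or rule that would yield such a declaration. The wording invites that reading, but the plan does not require it.
- *That 17 is too few, or that a comparator is missing.* Neither is an error in a declared first-in-man, single-arm, phase I study whose objective is to assess.
- *That the plan wrongly omits confidence intervals or a precision statement.* Only an article is at hand. The full protocol or the analysis plan may contain them, so their absence here is not a fault.
- *That safety is reported as raw counts only.* Percentages by category are planned, with grade, seriousness, relatedness and outcome recorded for each ADE. An independent data monitoring committee also reviews accruing data.

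What the defence does not remove is the mismatch itself. The abstract states an aim for the primary endpoint that differs from the stated primary objective and that the design cannot meet. An analysis plan could add intervals, but these would only make the limits visible.

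**Conclusion.** The point holds as a mismatch between a stated aim and the design. The abstract promises a demonstration of safety. The primary objective promises an assessment, and a single-arm study of 17 with no acceptable ADE rate can provide only that.

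At its most favourable, 0/17, the result is compatible with a true risk of up to 16.2% (one-sided 95%) or 19.5% (two-sided exact 95%). An event with a true risk of 5% would be missed altogether 42% of the time.

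These figures rest on the 95% level and the zero-event case, both chosen for this check, and on all 17 participants being implanted and followed for 12 months. They apply to any single category of ADE, whether of any grade or serious only. The two limits follow different conventions and should not be merged into one range.

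Severity is minor to modest. No endpoint, analysis or sample size is wrong; what needs limiting is what the trial may say it has shown.

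**What to change.** 1. In the abstract, replace the aim of demonstrating safety with wording that matches the primary objective: either to assess safety and tolerability, or to describe and estimate the 12-month rate of device-related and serious events.
2. Give the main percentages for ADEs and serious ADEs planned under Data collection with exact (Clopper-Pearson) 95% intervals, using implanted participants as the denominator. The article makes a separate summary of serious events depend on enough of them occurring. The line is worth showing even at zero, because the interval tells the reader most there.
3. Optionally, add one sentence under Sample size: 17 implanted participants with no event would still allow a true risk of up to 16.2% (one-sided 95%) or 19.5% (two-sided 95%).

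The cost is a change of wording and one column of intervals. Sample size, endpoint and follow-up stay as they are. The only downside is a more modest claim.

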## Introduction

Peripheral nerve injuries are a common occurrence, with approximately 9000 cases in the UK occurring each year. Most are in a predominantly young and working population. Where surgical reconstruction is required to repair the peripheral nerve injury, techniques employed have changed little in the last 50–60 years
^1^ with many factors influencing the outcomes, such as age of patient, timing, level and extent of injury, method of repair and the surgeon’s skill
^2^.

Despite advances in microsurgical nerve repair techniques, functional recovery is often poor, and can result in impaired hand sensation, reduced motor function and frequent pain and cold intolerance. This can have a profound and permanent impact on the patient’s recovery and subsequent quality of life. Nerve repair has significant health, social and cost implications with the treatment and rehabilitation of an employed person, estimated to be €51,238
^3^.

Peripheral nerve injury usually presents with nerve stumps that can be approximated in surgical repair: direct, end-to-end suture repair of the epineurium (neurorrhaphy). Excessive tension over the suture line leads to poor results
^4^; therefore, when the nerve stumps cannot be approximated without tension, an alternative surgical method is required.

Where the nerve gap exceeds more than 5 mm, there are two fundamental options, either ‘nerve grafting’ or ‘tubulisation’ using a bridging material
^5^. This study will examine the first-in-man use of a new nerve conduit device ‘Polynerve’ to repair small nerve gaps in digital sensory nerves of the hand. Polynerve is a degradable co-polymer of poly-ε-caprolactone (PCL) and Poly-L-lactic acid (PLLA) which is shaped as a cylinder with a novel internal lumen consisting of a specific micro-grooved architecture.

### Current treatments

In the presence of a nerve gap, the gold standard is to use the patients’ own nerve tissue (autograft) to bridge the gap in the damaged/severed nerve. The sural/antebrachial cutaneous/posterior interosseus nerves are favourable and commonly used donor nerves to use in such repair. As the harvested nerve undergoes Wallerian degeneration, the autograft functions as a guide or scaffold, with the advantage of the presence of Schwann cells creating a conducive environment for regenerating axons
^1^.

However, there are inherent problems in this approach: a second surgical site and sensory deficit at the donor site, limitation of material, possible neuroma formation and graft mismatch
^5–
8^.

This has prompted research on the use of bio-engineered nerve conduits as an artificial means of guiding axonal regeneration. These conduits function as a guide for axonal growth and help maintain an internal environment for nerve regeneration. Currently available nerve conduits are not ideal: several are prepared from inert non-biodegradable materials or from natural collagen with inherent risks of disease transmission and immuno-rejection. Furthermore, the high cost of these devices limits their appeal to the United Kingdom’s National Health Service, where cost-effectiveness is paramount. Despite advances in bioengineering, commercially available conduits to date have not been able to match the results of the current clinical gold standard, i.e. that of reconstruction using a nerve graft.

### Review of peripheral nerve conduits

Nerve repair by tubulisation, in which the opposing nerve stumps of a transected nerve are enclosed in a tube (nerve guide conduit), was first described in 1880 when a decalcified bone segment was used to provide a pathway between the ends of a severed nerve
^9^. The tubulisation technique is designed to protect the nerve from the surrounding tissue and potential scar tissue, as well as providing mechanical support, directional guidance for axonal sprouting and an environment permissive to nerve development and regeneration
^2,
10^. A number of reviews have been published in which the ideal features of a nerve guide conduit are considered; that is, readily available in appropriate sizes, sterilisable, easily implantable, biocompatible, and with appropriate physical and mechanical characteristics to be flexible and suturable, yet able to withstand compression or collapse
^2,
11^.

### Non-resorbable peripheral nerve guidance conduits

The first generation of artificial nerve guide conduits for clinical application were non-resorbable silicone tubes however in many cases further surgeries were required to remove the tubes following nerve regeneration due to the risk of nerve compression
^6,
12^. Although silicone and expanded polytetrafluroethylene (ePTFE) have both been used clinically for nerve repair, use of non-resorbable materials in this indication has been associated with chronic nerve compression, decreased axonal conduction and fibrosis
^8,
11^ as well as presenting a risk of chronic foreign body reaction with excessive scar tissue formation
^7^.

As a result of the problems experienced, use of non-resorbable materials in nerve guide conduits has significantly declined. Furthermore, in describing the design criteria for nerve guidance conduits the FDA, who have responsibility for regulatory approval of medical devices for use in the USA, have stated that the material used must be biodegradable
^10^. Conduit dimensions are also highlighted as a critical design feature as diameter and wall thickness are believed to influence the rate of regeneration as well as potentially compressing the growing nerve if the diameter is inadequate
^10^.

### Resorbable natural peripheral nerve guidance conduits

Resorbable nerve guidance conduit devices may be derived from natural or synthetic materials. Natural polymer-based devices are predominantly derived from collagen because of the inherent biocompatibility and relative abundance of this protein
^13^. A number of Type I bovine collagen derived nerve guidance conduits and wraps have gained regulatory approval for use in peripheral nerve injury: i.e. NeuraGen® (Integra, FDA 510 (k) approval 2001; CE mark 2003), NeuroMatrix®, and NeuroFlex® (Stryker, FDA 510(k) approval 2014)
^10^.
*In vivo* studies with NeuraGen® demonstrated equivalent functional performance in entubulation repair compared to use of standard nerve autograft and direct suture repair
^14^. NeuraGen® clinical data from several prospective and retrospective studies have been published demonstrating clinical safety and efficacy
^15–
17^. Although there appeared to be acceptable outcomes in small sensory nerve repair, mixed motor/sensory nerves fared comparatively poorly
^18^.

### Resorbable synthetic peripheral nerve guidance conduits

Synthetic biodegradable polymers offer many advantages in the fabrication of devices for peripheral nerve injury. The materials are readily available and can be engineered to modify physical and mechanical characteristics, such as strength, permeability and degradation rate as well as cell attachment and proliferation by using physical or chemical modifications
^12^.

### Polyglycolic acid

Polyglycolic acid conduits were the first to be used in clinical studies for peripheral nerve repair
^7^. There is preclinical and clinical data for Neurotube® (Synovis, CE mark 1995; FDA 510 (k) 1999) demonstrating efficacy in gap defects in animal models up to 30 mm and comparable efficacy to primary or nerve graft repair in randomised clinical trials
^19^. Although most safety and efficacy data exist for Neurotube® compared to other nerve graft conduits, the rapid degradation, concomitant reduction in mechanical strength and acidic degradation products are limiting factors to its use
^10^.

### Poly-lactic acid (PLA) and PCL

PLA and PCL are biocompatible and approved for use in numerous biomedical applications. Polylactide (L- and DL- forms) copolymerised with PCL have found utility in nerve guide conduits and Neurolac® (Polyganics, FDA 510 (k) 2003; CE mark 2004), consists of a poly (65/35(85/15 L/D) lactide ε-caprolactone) phospho-ester. Neurolac® has extensive pre-clinical
*in vivo* data, and in randomised clinical trials Neurolac® is reported to have comparable efficacy to gold standard autograft in defects up to 20 mm
^20^. Known adverse events associated with the use of a Neurolac® nerve guide include but are not limited to: failure to provide adequate nerve regeneration at sites where too much tension or compression occurs; failure to provide adequate/complete nerve regeneration; transitory local irritation; infection; allergy and delayed wound healing. Limitations are reported to be the high rigidity and inflexibility of the device. In comparison to Neurolac®, Polynerve has greater tensile strength, flexibility and less acidic degradation, whilst the microgrooves on the internal lumen provide a protected environment for ingress of Schwann cells (the supportive cell of the peripheral nervous system), which align on the micro-patterned grooves and aid subsequent nerve regeneration.

### Preclinical and clinical trials

Experimental
*in vitro* studies have demonstrated that PCL/PLA blended films are able to support the attachment and growth of Schwann cells
^21^. These cells are key players in nerve regeneration through delivery of neurotrophic factors and extracellular matrix proteins. Furthermore, the microgrooved internal lumen of Polynerve promotes neural regeneration
^22^ and Schwann cell alignment
^23^ to guide the nerve regeneration process. Subsequent
*in vivo* studies on rat sciatic nerve gap of 10 mm demonstrate comparable efficacy of regeneration to nerve graft (current clinical gold standard) in both short (3 week) and long (16 week) timepoints
^22^.

Moreover,
*in vitro* and
*in vivo* evidence demonstrates an improved biological response of the specific micro-grooved architecture of Polynerve when compared to no grooves. Therefore, it is likely to be at a biological advantage when compared to the use of Neurolac® (Polyganics BV) which contains no internal lumen architecture within which to guide the neural regeneration. In randomised clinical trials, Neurolac® is reported to have comparable efficacy to gold standard autograft in defects up to 20mm
^20^. This device is made of similar polymer materials but at a different PCL:PLA ratio. Whilst Polynerve is 4:1, Neurolac® is 1:1 which confers a more rapid degradation and mechanical problems in particular a lack of flexibility. For these reasons, we expect Polynerve to be a superior nerve repair conduit in clinical use.

## Primary objective

To assess the safety and tolerability of use of the polymer biomaterial nerve conduit to repair a sensory nerve transection of the hand.

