### Known and potential risks of study procedures

The potential risks to all participants undergoing sensory nerve repair include abnormal scar formation (hypertrophy/keloid), delayed wound healing, pain related to the wound site, neuroma formation, altered sensation of the skin around the wound (paraesthesia), no improvement in recovery of sensation, surgical site infection and bleeding requiring surgery (haematoma). Depending of the severity of these events some may require further surgery.

The additional potential risks to study participants receiving our polymer nerve conduit are persistent infection, allergy to the polymers PCL/PLA, local irritation and extrusion of the device. Some such risks may require surgical removal of the Polynerve device. These complications have not occurred in any animal studies conducted to date.

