### Harms

Expected AEs which may occur as a result of the surgical procedure include:

•   Bleeding from the wound site (haematoma)

•   Infection of the wound site

•   Abnormal scar formation (hypertrophy/keloid)

•   Delayed wound healing

•   Pain related to the wound site

•   Altered sensation of the skin around the surgical site (paraesthesia)

•   Development of neuroma

Expected ADEs which may occur as a result of the medical device under investigation are:

•   Intractable infection of the surgical site

•   Allergy to the polymers PCL/PLA

•   Local irritation

•   Extrusion of device through the wound

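### The primary objective includes tolerability, but the primary outcome covers safety only, summarised as adverse device effects, so tolerability has no defined outcome

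*Protocol article*

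**What the plan says.** The Primary objective section reads: "To assess the safety and tolerability of use of the polymer biomaterial nerve conduit to repair a sensory nerve transection of the hand". The Abstract gives the endpoint as "The primary endpoint is safety of the device", and the Data collection section gives the outcome as "The primary outcome is safety following implantation of the Polynerve device", to be assessed by the number and Clavien-Dindo grade of ADEs.

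The same section provides for wider capture of events: "all adverse events (AE) will be assessed and recorded by the P.I" or a deputised co-investigator, with a causality assessment for each. It adds: "Safety information and all concomitant medications (that are associated with the surgical procedure) will be reviewed at each follow up visit". The summaries it then describes are of ADEs: participants with each ADE, and numbers and percentages by ADE category. Serious events are summarised separately if enough occur.

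The Harms section lists "Pain related to the wound site", neuroma and altered sensation as expected AEs of the surgery. Its separate list of expected ADEs contains intractable infection, polymer allergy, local irritation and extrusion. The section on known and potential risks divides them the same way, placing "pain related to the wound site, neuroma formation, altered sensation of the skin around the wound (paraesthesia") among the risks of any sensory nerve repair.

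Table 2 schedules concomitant medication, safety reporting, sensory outcome assessment, ultrasound and wound examination. It has no row for a symptom rated by the participant.

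**The concern.** A primary objective with two parts needs an outcome for each part, and here only safety has one. The events that bear most directly on how well participants tolerate the repair, namely pain, neuroma and altered sensation, sit on the procedure list, while the described summaries are built on the device list. Whether an episode of pain enters the primary summary may therefore depend on a causality judgement made without blinding, in a single-arm study where every participant has a fresh hand wound.

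At stake is what the report of this first-in-man study can say. With 17 participants and no formal power calculation, its value lies in a complete description. It could report on tolerability without having fixed what the word means, and non-serious pain attributed to surgery could be recorded on the forms yet not appear in the main table.

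**Working it through.** No power, alpha or effect size is involved and the plan gives no figure to reproduce. The check sets the sections of the protocol article against one another.

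1. **Objective against outcome.** The Primary objective section names safety and tolerability. The Abstract and Data collection name safety. Mentions of tolerability in the article: 1. Outcomes assigned to it: 0.

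2. **What is recorded.** Data collection has all AEs recorded. Table 2 marks safety reporting and concomitant medication at baseline and at 1 week, 2 weeks, 3, 6 and 12 months, which is 5 of 5 follow-up visits. Wound examination is also at all five. Wound pain can therefore be recorded as an AE at every follow-up visit.

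3. **What is summarised.** The specified end-of-study summaries count ADEs, plus serious events if there are enough. The Statistical methods section says only that primary outcome data will be described and summarised. A non-serious episode of wound pain attributed to the operation is an AE and not an ADE. It passes step 2 but is not named in any summary at step 3.

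4. **What is known about its course.** The listed case report form variables are for each ADE and include onset, the Clavien-Dindo grade of maximum intensity, relatedness and outcome. One maximum grade per event does not show a course over time, so later worsening could sit behind a higher early post-operative peak. The Discussion says the device is designed to be fully absorbed 18 months after implantation. Follow-up ends at 12 months, so absorption is still under way throughout, and its last 18 − 12 = 6 months are not observed.

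5. **Other measures.** The secondary outcomes (two-point discrimination, WEST and locognosia) test sensation. None rates pain or cold intolerance. Scaled pain or cold-intolerance assessments in the seven columns of Table 2: 0.

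6. **Size of the remedy.** One rating at baseline and five follow-up visits in 17 participants is 17 × (1 + 5) = 102 readings per item at most. This measures the added burden and not the size of the defect.

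**The case against.** The strongest reply is that pain is already captured. All AEs are recorded, safety and surgery-related medication are reviewed at every follow-up visit, and wound pain, neuroma and paraesthesia are pre-listed as expected events. For ADEs the forms hold grade, relatedness and outcome, and local irritation is already an expected ADE and so inside the primary outcome. This stands. A reader might infer that no visit captures pain, or that tolerability cannot be answered at all. The documents support neither, since recorded AEs, their causality and the medication reviews give some information on it.

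A reader might also infer that cold intolerance is a harm the protocol names for the device or the procedure. It is not. The Introduction says that poor recovery "can result in impaired hand sensation, reduced motor function and frequent pain and cold intolerance", which is background on nerve injury, and cold intolerance appears on neither the risk list nor the Harms list. Rating it is an option and not the repair of a contradiction.

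Two further replies have weight. First, the article condenses a full protocol that is not shown and may define tolerability or the questions asked at each visit. That excuses missing detail, but not an objective and an outcome that are both stated here and do not match. Second, the article may use the term ADE loosely: it plans a category of causally related ADEs and records relatedness to the device or another procedure. The summaries may therefore be meant to cover more than device-related events. This is why the claim is that procedure events may be left out, and not that they will be.

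Finally, a 0-10 score without a comparator cannot separate ordinary post-operative pain from pain due to the conduit, and a baseline score in an acute injury mainly reflects the injury. That is correct, and it limits what the ratings can be used for.

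**Conclusion.** The mismatch between objective and outcome is real and modest. Tolerability is part of the only primary objective and has no defined outcome. The specified primary summaries may omit pain and neuroma attributed to surgery, and no scheduled rating shows how pain develops over 12 months. Recording of safety events is not in question. The gap lies in definition, summary and scaling.

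This rests on two assumptions: that ADE in the summaries carries its ordinary meaning of a device-related event, and that the unseen full protocol does not define tolerability separately. If either is wrong, the gap narrows to wording that still needs to be aligned. The correction is worth making because it is cheap and lets the trial answer its stated objective.

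**What to change.** In the primary outcome text of the Data collection section:

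- Define tolerability as all-cause AEs, naming wound pain, neuroma and paraesthesia, summarised by participant alongside the ADE summaries.
- Add a 0-10 pain rating for the injured digit at baseline and at the existing 1-week, 2-week, 3-, 6- and 12-month visits, reported descriptively as individual profiles. A 0-10 cold-intolerance rating at the same visits is optional.
- State that the ratings describe the course of symptoms and are not used alone to attribute them to the conduit.
- Add the rating to Table 2.

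If the sponsor does not want to collect this, remove tolerability from the Primary objective section so that objective and outcome agree.

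The cost is one or two short questions at existing visits, at most 102 readings per item, and a descriptive table. No new visit, procedure or staff is needed. The downside is a small questionnaire burden and a safety picture that may look less favourable.
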